### 5 Number of Participants

Indicate the total number of participants to be recruited and enrolled

- Provide a rationale for the proposed enrollment number
- What percentage of screened individuals will likely qualify for the study?

**We will screen ~300 obese Latino youth for prediabetes and anticipate that 120 will meet eligibility into the trial. These estimates are based on rates of elevated 2-hour glucose in our current study (~40% exhibit 2-hour glucose  $\geq 120$  mg/dl).**

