**Health Screening and Metabolic Phenotyping:** Potential participants will arrive at the ASU Clinical Research Unit at ~8:00 AM after an overnight fast for initial screening including a brief health history, height and weight measurement to calculate BMI percentile, and a standard 75g OGTT for fasting and 2-hour glucose (assessed by SonoraQuest Laboratories). Participants meeting inclusion criteria (described above) will return within 4 weeks of the screening OGTT for baseline testing to include in-depth medical and family history (including in utero exposure to gestational diabetes) and a brief physical exam. Height, weight, and waist circumference will be measured to the nearest 0.1cm, 0.1 kg, 0.1cm, respectively. Sitting blood pressure will be measured in triplicate using an appropriately-sized cuff on the right arm after 5 min of rest. A fasting lipid panel will be collected to measure cholesterol (Total, HDL, and LDL), triglycerides, and HbA1c. These assessments follow current recommendations for screening in obese youth, will be used in the curriculum to discuss the health risks of obesity, and are an important and meaningful benefit to families.

**Glucose Tolerance and Insulin Sensitivity (Aim 1):** Glucose tolerance and insulin sensitivity will be assessed by a 75 gram OGTT with multiple blood sampling for insulin glucose. Blood samples will be collected from an in-dwelling catheter at -15', -5', 30', 60', 90' and 120' for measurement of plasma glucose (glucose oxidase, YSI INC., Yellow Springs, OH) and insulin (ELISA, ALPCO Diagnostics, Windham, NH). At time 0', participants will ingest 75 grams of glucose in solution. Improvements in glucose tolerance will be assessed by decreases in 2-hour glucose levels (primary outcome) while changes in insulin sensitivity will be estimated by the whole-body insulin sensitivity index. For the purposes of this study, glycemic status will be defined as "Normal" (fasting glucose <100 mg/dl and 2-hr glucose <120 mg/dl), "Prediabetic" (fasting glucose ≥100 mg/dl or 2-hr glucose ≥120 mg/dl), or "Diabetic" (fasting glucose ≥126 mg/dl or 2-hr glucose ≥200 mg/dl). **NOTE:** Youth identified as "diabetic" at any point in the study will be referred for follow-up care and given the option to continue with the study with clearance from their physician.

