## BIOSCIENCE INSTRUCTIONS AND TEMPLATE

NUMBER

HRP-503b

DATE

3/22/2022

PAGE

11 of 13

**Specific Aim 1:** We will test the hypothesis that adolescents who complete the intervention will exhibit significantly greater short-term and long-term improvements in glucose tolerance and increases in insulin sensitivity compared to UCC. ANCOVA models will use pretest measures as a covariate and the experimental groups (i.e., intervention vs. UCC) for comparisons. Separate analyses will be conducted for 6- and 12-months. We will explore interactions between the covariate (baseline measure) and group to determine whether adolescents with lower baseline scores differentially benefit from the program. Assuming no interaction is found, we will examine the main effect of group assignment on the outcome measure after adjusting for baseline. We will also conduct repeated measures ANCOVA models to examine differences in the effect of the intervention on primary outcomes between 6- and 12-month time points.

**Specific Aim 2:** We will use the same ANCOVA models described above to examine the effects of the intervention on general and weight-specific QoL. Results will indicate whether adolescents who were randomized to the intervention report greater increases in QoL compared to adolescents randomized to UCC.

**Specific Aim 3:** We will explore the mediating effects of changes in total body composition on changes in T2D risk markers by path analysis. Each mediation model will include three variables: (1) experimental group membership represented by dummy codes, (2) a mediator measure (e.g., fat mass), and (3) an outcome measure. The model specifies direct paths from group membership to the mediator and outcome. Path coefficients and standard errors for these paths will be estimated. Effect size measures will include: (1) direct effects on outcome and (2) mediated or indirect effects on outcome. The latter will be estimated using path coefficient estimates with standard errors.

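### Aim 1 names no analysis scale for the insulin sensitivity index and places a baseline-by-group check ahead of its main effect; if the index behaves multiplicatively, untransformed ANCOVA raises false interactions and loses power

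*Supplement*

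**What the plan says.** Section 8 of the protocol (Glucose Tolerance and Insulin Sensitivity) names the decrease in 2-hour glucose as the primary outcome and adds that "changes in insulin sensitivity will be estimated by the whole-body insulin sensitivity index". The index comes from glucose and insulin sampled during the OGTT.

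Section 16, Specific Aim 1, gives a single analysis for both measures: "ANCOVA models will use pretest measures as a covariate and the experimental groups (i.e., intervention vs. UCC) for comparisons". It continues: "Separate analyses will be conducted for 6- and 12-months". Before the group comparison there is a check: "We will explore interactions between the covariate (baseline measure) and group to determine whether adolescents with lower baseline scores differentially benefit from the program". The next sentence makes the comparison follow from it: "Assuming no interaction is found, we will examine the main effect of group assignment on the outcome measure after adjusting for baseline". Repeated-measures ANCOVA models are also planned.

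The protocol states no transformation, check of distribution or variance, robust standard error, or level for the interaction test. It does not say what will be reported if an interaction is found. No separate SAP is shown.

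**The concern.** An index built from OGTT glucose and insulin may well vary in proportion to its level, so that a treatment multiplies it instead of adding a constant. If so, ordinary least squares on the untransformed index has two problems.

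- Residual spread grows with the baseline index, so the usual standard error for the baseline-by-group term is too small and the check signals too often even when treatment does nothing.
- A benefit that is the same percentage for everyone gives a steeper slope in the intervention arm. Youth with a higher starting index then appear to gain more in absolute units, although the relative gain is uniform.

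Both matter because the plan takes up the main effect only after the interaction question is settled. Insulin sensitivity is one of the two measures in Aim 1. A misleading interaction could become the headline for it, and the comparison of arms would be less precise than the same data allow.

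**Working it through.** **The plan's own figure.** The only sample-size figure is a screening yield: "We will screen ~300 obese Latino youth for prediabetes and anticipate that 120 will meet eligibility into the trial", based on about 40% with elevated 2-hour glucose. 300 × 0.40 = 120, which reproduces. No alpha, power, effect size or SD is given, so no power figure can be reproduced.

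**Inputs.** From the protocol: 120 participants, ANCOVA with baseline as covariate, a baseline-by-group check. Assumed: 1:1 allocation (60 per arm), two-sided 5%, log-normal index, log-SD 0.3–0.8 (CV 0.31–0.95), baseline to follow-up correlation on the log scale 0.3–0.8, and a constant-ratio effect sized for 80% power on the log scale.

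**Why variance rises.** Write s for the log-SD and ρ for the correlation. Under this model the mean and the SD of follow-up given baseline X are both proportional to X^ρ. With s = 0.5 and ρ = 0.6, residual SD at one log-SD above the baseline median is exp(2 × 0.5 × 0.6) = exp(0.6) = 1.82 times that at one log-SD below.

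**Effect size.** log ratio = (1.960 + 0.842) × s × √(1 − ρ²) × √(4/n). With s = 0.5, ρ = 0.6, n = 120: 2.802 × 0.5 × 0.8 × 0.1826 = 0.205, a ratio of 1.23. The slope on the untransformed scale is then 1.23 times as steep in the intervention arm.

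**Simulation** (n = 120, 10,000 trials per row, ordinary least squares):

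| log-SD | ρ | Ratio | False interaction, no effect (raw) | Interaction, constant ratio (raw) | Interaction, constant ratio (log) | Power raw | Power log |
|---|---|---|---|---|---|---|---|
| 0.4 | 0.7 | 1.16 | 13.7% | 20.0% | 5.2% | 74.0% | 78.9% |
| 0.5 | 0.6 | 1.23 | 16.1% | 21.7% | 5.0% | 72.0% | 79.5% |
| 0.7 | 0.5 | 1.36 | 19.7% | 25.1% | 5.1% | 66.4% | 79.3% |
| 0.7 | 0.7 | 1.29 | 27.4% | 35.5% | 4.7% | 62.7% | 78.7% |
| 0.8 | 0.8 | 1.28 | 36.9% | 46.2% | 5.2% | 58.8% | 78.9% |

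At the mild corner (log-SD 0.4, ρ = 0.5) the false-interaction rate is about 10% and the power loss about 4 points. At log-SD 0.3 the figures are 6–11% and 2–3 points. With 96 analysed (20% loss, an assumption), false interactions for log-SD 0.4–0.7 and ρ 0.5–0.7 are 10–27%. Type I error of the untransformed main-effect test is 4.5–5.3% throughout.

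**Which feature is responsible.** With a skewed baseline but constant error variance, whether the errors are skewed or normal, the false-interaction rate is 4.2–5.6%. With HC3 errors on the untransformed log-normal data it is 5.2–5.7%. The cause is therefore variance rising with baseline.

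**If the effect is additive in index units.** For log-SD 0.4–0.8 the log-scale interaction check signals in 8–60% of trials. Main-effect power on the log scale is still higher, 92–100% against 80–82%.

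**If a significant interaction means the main effect is not reported.** The chance that a constant-ratio effect passes the check and is also significant is 65%, 54% and 36% untransformed, against 75–76% on the log scale (log-SD/ρ of 0.4/0.5, 0.5/0.6 and 0.7/0.7). This depends on a reading that the protocol does not spell out.

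**The case against.** The best case against acting is that the protocol is silent on scale. It nowhere says that the index will be left untransformed; section 16 gives a paragraph per aim, and transformations and residual checks are often left to a SAP. That is fair as a description of the text. But an analyst who follows the paragraph literally fits the untransformed index, and because the interaction check comes first, the scale affects more than detail.

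A second objection is that every percentage depends on a distribution, SD and correlation that the protocol does not supply. This stands. At log-SD 0.3 the loss is small, and eligibility limited to obese youth with raised glucose could narrow the spread.

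Several stronger readings are tempting and are not supported:

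- A reader might infer that skewness alone produces the false interactions. It does not; with constant error variance the rate stays at about 5%.
- A reader might infer that taking logs always removes the interaction. It does so only when effect and errors are proportional; under an additive effect the log scale can create one.
- A reader might infer that the plan discards the main effect whenever the check is significant. The text calls the check exploratory, sets no level for it and leaves that case open, and the repeated-measures models carry no such condition.
- A reader might infer that the trial's main conclusion is at risk. The named primary outcome is 2-hour glucose, and the untransformed group test of the index keeps its type I error.

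**Conclusion.** The point holds in conditional form and is worth correcting, but it does not threaten the validity of the trial. The plan leaves the scale of the insulin sensitivity index unspecified and puts an interaction check in front of its main effect. If the index is multiplicative, the untransformed analysis gives false interactions in about 10–28% of null trials and costs about 4–16 points of power (log-SD 0.4–0.7, ρ 0.5–0.7, 60 per arm). Over the wider inputs this is about 6–37% and 2–20 points. The direction is the same across that grid; the size cannot be fixed from the protocol. The harm is lost efficiency and a misleading subgroup signal on an outcome not labelled primary.

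**What to change.** Amend Specific Aim 1 in section 16 to state four things:

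1. The insulin sensitivity index is analysed as its natural logarithm, with log baseline as covariate, in the 6-month, 12-month and repeated-measures models and in the baseline-by-group check. The same log index is used where it is the outcome in the Aim 3 path models.
2. The effect is reported as a ratio of geometric means with a 95% confidence interval.
3. The baseline-by-group check uses heteroscedasticity-robust (HC3) standard errors and is exploratory.
4. The baseline-adjusted main effect is reported whatever that check shows.

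Item 4 is needed because a log-scale check still signals about 5% of the time by chance, and more often if the effect is additive. HC3 errors correct the standard error but do not remove a real difference in slopes.

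The cost is a few sentences of analysis text and no new data. The drawbacks are that the effect is reported as a ratio instead of in index units, and that an effect that is truly additive may itself appear as an interaction on the log scale.

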**Intervention (Physical Activity):** The PA intervention includes structured and unstructured components. The structured PA curriculum is led by YMCA instructors and delivered 2 days/week to groups of 8-10 youth (both boys and girls) for 60-minutes each. Classes include aerobic and resistance exercises delivered in a progressive manner with the first 2-4 weeks focusing on motor skill acquisition, exercise confidence, developing a fitness base, and building camaraderie among participants. Aerobic exercises include group activity classes (e.g. spinning and cardio kick-boxing) with the goal of maintaining heart rates > 150 BPM. Real-time heart rate monitoring and rate of perceived exertion are used to monitor and document exercise intensity throughout the program. This exercise intensity was selected for the established effects on improving metabolic health in obese youth. Resistance exercise includes circuit training using age and size appropriate equipment and is incorporated because our previous studies suggest this form of exercise is both enjoyable and metabolically beneficial for obese youth. In addition to structured PA classes, youth are 'prescribed' an additional day of unstructured PA of at least 60-minutes with a family member or peer in the program. This allows for flexibility in pursuing preferred activities that can be done at the YMCA or elsewhere in the community in order to promote social support, role modeling, bonding among youth and families, and facilitate sustainability.

**Booster Sessions:** Three booster sessions (months 7, 8, and 9) following the completion of the intensive lifestyle period will be held to support the maintenance of healthy lifestyle behaviors, address any challenges encountered, and promote successes achieved. Post-intervention clinical measures will be returned to participants at the first session and changes in health status will be discussed in the context of maintaining healthy lifestyle behaviors.

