**Usual Care Control (UCC):** Participants randomized to the UCC will meet with a pediatric endocrinologist ([name]) to review laboratory results at baseline and 6-months. In addition, UCC participants will meet with a registered dietitian ([name], RD) who will provide general lifestyle counseling on healthy eating and PA at baseline and 6-months. This approach mirrors local standards/current practice for obese youth referred to weight management. Randomizing obese children with prediabetes to a true control condition is not ethical as our previous and current studies suggest rapid decompensation occurs in this group. To ensure retention in UCC participants, the research team will contact youth via phone, text, or email (youth/parent preference) on a monthly basis throughout the entire study period (months 1-12). Upon completion of the study, control youth will be offered an abridged version of the intervention and a 1-year membership to the YMCA. Although it would be preferable to offer the entire intervention to UCC youth, this is not feasible due to study costs and time constraints.

**Post-intervention Follow-up:** All youth, regardless of group, will be contacted on a monthly basis via phone, text, or email to enhance retention and ensure availability for testing 12-months after baseline.

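### The 12-month ANCOVA discards the observed 6-month glucose, so the long-term effect can be biased if dropout depends on that value; one likelihood-based longitudinal model would use it

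*Supplement*

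**What the plan says.** Section 16, Specific Aim 1, compares the arms by ANCOVA with the pretest value as covariate: "Separate analyses will be conducted for 6- and 12-months". It then adds a second model: "We will also conduct repeated measures ANCOVA models to examine differences in the effect of the intervention on primary outcomes" from one follow-up visit to the other. How that model is estimated, and whether it keeps youth with one follow-up visit missing, is not stated. The Aim 1 hypothesis is worded for adolescents who complete the intervention. The primary outcome in section 8 is the fall in 2-hour glucose.

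Sections 8 and 9 describe what happens between the two follow-up visits:

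- Usual care youth meet an endocrinologist "to review laboratory results at baseline and 6-months".
- Intervention youth attend boosters in months 7, 8 and 9. "Post-intervention clinical measures will be returned to participants at the first session".
- Youth found diabetic at any point are referred and "given the option to continue with the study with clearance from their physician".
- Section 9 indicates that no further visits are scheduled after a withdrawal.
- Both arms are contacted monthly to limit loss.

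**The concern.** An ANCOVA of the 12-month value on baseline and group can include only youth who have a 12-month value. Anyone seen at 6 months and then lost contributes nothing, although the 6-month glucose is on file and predicts the missing value. If leaving after month 6 depends on that glucose, the youth who remain in each arm are a selected group, and adjusting for baseline alone does not undo the selection.

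The protocol makes such dependence possible, because families know the 6-month result, hear it in a different setting by arm, and face a decision about continuing if diabetes is found. The repeated-measures ANCOVA does not settle this. Its stated target is the difference between visits, and in its classical form it drops anyone with a visit missing.

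At stake are the long-term efficacy claim of Aim 1, the 6-versus-12-month comparison, and the Aim 4 cost-effectiveness ratio, which uses 12-month 2-hour glucose. The 6-month ANCOVA is not exposed to this mechanism, because the results are given out afterwards.

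**Working it through.** **1. What the plan's own figures supply.** Section 5 states: "We will screen ~300 obese Latino youth for prediabetes and anticipate that 120 will meet eligibility into the trial", because about "40% exhibit 2-hour glucose" at or above 120 mg/dl. 300 × 0.40 = 120, so the figure reproduces. It is a screening yield. No SD, effect size, dropout rate or retention target is given, so every input below other than the 120 is an assumption.

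**2. Form of the bias.** Approximately,

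bias = γ × (Δ_int − Δ_ucc)

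where γ is the slope of the 12-month on the 6-month value given baseline, and Δ is how far the mean baseline-adjusted 6-month value of those who stay differs from that of the whole arm. If selection is equal in the two arms, the terms cancel. A treatment effect makes them slightly unequal even under one rule, because the arms then sit at different glucose levels.

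**3. Large-sample simulation, SD units.** Assumed: 1:1 allocation, total SD 1, baseline correlation 0.5, partial 6–12-month correlation 0.5, true effect −0.40 at both visits. The log-odds of leaving are −1.5 (18% at the average) plus 0.8 per SD of 6-month glucose in an affected arm, with the sign reversed where low-glucose youth leave. Dropout is about 17–24% overall.

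| Who tends to leave after month 6 | 12-month ANCOVA | Bias | Using the 6-month value |
|---|---|---|---|
| High glucose, same rule in both arms | −0.39 | 0.01 | −0.40 |
| High glucose, usual care only | −0.34 | 0.06 | −0.40 |
| High glucose, intervention only | −0.45 | −0.05 | −0.40 |
| High glucose in usual care and low glucose in intervention | −0.27 | 0.13 | −0.40 |

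With no treatment effect, the same rule in both arms gives a bias of about 0. Arm-specific rules still give about 0.06 (one arm) and 0.12 (opposite rules).

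**4. A second simulation, in mg/dl.** Assumed: SD 25 or 35, baseline 2-hour glucose 120–199, 6–12-month residual correlation 0.3 or 0.6, true 12-month benefit 10 unless noted. Positive bias means benefit understated.

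- Only youth at or above 200 mg/dl at 6 months leave, same rule in both arms: 0.05–0.30 (SD 25) and 0.24–1.14 (SD 35).
- Only such controls leave: 0.13–0.38 (SD 25) and 0.94–2.02 (SD 35).
- Graded dropout of about 17–25%, same rule in both arms: 0–0.84, and 0 with no effect.
- Opposite rules by arm, 20–27% dropout: 1.8–5.6, including runs with no effect.

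Using the 6-month value brought the bias to zero within simulation noise of about 0.1 mg/dl throughout.

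**5. Scale against sampling error.** At an assumed 80% retention, 120 × 0.80 = 96, or 48 per arm. SE ≈ √(2/48) × √(1 − 0.5²) = 0.204 × 0.866 = 0.18 SD. The one-arm bias is about a third of an SE (0.06/0.18), and the opposite-rules bias about 0.7 of one (0.13/0.18).

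**6. Precision.** With retention p and partial correlation r, the variance ratio of the joint model to the separate ANCOVA is 1 − (1 − p)r². For p = 0.8: r = 0.5 gives 1 − 0.2 × 0.25 = 0.95, and r = 0.6 gives 1 − 0.2 × 0.36 = 0.93. The saving is about 5–7%.

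**The case against.** The strongest reply is that nothing in the protocol shows that youth leave because of a 6-month result. Being told a result is not a reason to leave. Monthly contact in both arms, payment at testing visits and help with transport all work against loss. If dropout follows the same rule in both arms, the bias is negligible, and with no treatment effect it vanishes. All of this stands. It means that bias is possible, not shown.

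A reader might go further and infer that the 12-month effect is biased, or that youth with the worst glucose are the ones most likely to be missing. The documents support neither. Section 8 lets youth found diabetic continue.

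A reader might also infer that conversions to diabetes alone would hide several mg/dl. If 5–10% of usual care and 2–3% of intervention youth converted, all left, and each carried an 80 mg/dl excess (210 versus 130, assumed), the shift would be 80 × 0.03 = 2.4 to 80 × 0.07 = 5.6 mg/dl. But a youth lost after a 6-month finding is not expected to keep the whole excess. At partial correlation 0.5 it is about 40 mg/dl, which halves the shift to 1.2–2.8. The pairing of rates is also selective: 5% versus 3% gives 80 × 0.02 = 1.6 before halving. A conversion first seen at the 12-month visit is observed, not lost.

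It is also fair that a repeated-measures model is planned, and that a separate analysis plan, not shown, might hold missing-data detail. The point does not rest on that absence. It rests on the method that section 16 does state for the 12-month test, which leaves out the 6-month value.

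Finally, loss that is specific to one arm has another documented route. Under section 9, youth below 75% attendance (54 of 72 sessions) may be asked to leave, which can affect only the intervention arm. That is not a rule on glucose, so it adds to the case for a model in all randomised youth without proving this mechanism.

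**Conclusion.** The point holds as a weakness in the choice of analysis, worth correcting before the data are analysed. The stated 12-month ANCOVA discards an observed predictor of the missing outcome, and dropout may depend on that predictor. Under the assumed inputs the 12-month effect of −0.40 SD shifts by about 3% of its size under one common rule (0.01/0.40), by 12–15% if one arm only is affected (0.05–0.06/0.40), and by about a third under opposite rules (0.13/0.40). The shift can go either way: losing high-glucose usual care youth understates benefit, and losing high-glucose intervention youth overstates it. These figures rest on the assumed dropout, its dependence on 6-month glucose and the 6–12-month correlation. The documents give none of these, so the actual size and direction are unknown.

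**What to change.** Replace the separate and repeated-measures ANCOVAs for 2-hour glucose and insulin sensitivity with one likelihood-based longitudinal model in all randomised youth with any OGTT. Include baseline, group, visit and group-by-visit, with an unstructured covariance over 6 and 12 months. Take the 6-month, 12-month and 6-versus-12-month contrasts from that model. With baseline as a covariate, youth who have neither follow-up OGTT add nothing to the contrasts, so report their number by arm. The planned look at a baseline-by-group interaction can be kept in the same model.

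The model is valid if dropout depends on baseline, arm and 6-month glucose. Because it may also depend on values never observed, add a prespecified sensitivity analysis, for example multiple imputation with shifts that differ by arm, run over a stated range.

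The cost is a change of wording in section 16 and slightly more modelling. No visits, tests or participants are added, and 12-month precision improves slightly.

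### The baseline-adjusted group effect, including for 2-hour glucose, is planned only if no baseline-by-group interaction is found, and no analysis is defined otherwise

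*Supplement*

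**What the plan says.** Section 8 of the protocol (glucose tolerance and insulin sensitivity) makes the fall in 2-hour OGTT glucose the primary outcome. The analysis plan is in section 16. For Specific Aim 1 it runs in this order:

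- The model: "ANCOVA models will use pretest measures as a covariate and the experimental groups (i.e., intervention vs. UCC) for comparisons".
- The time points: "Separate analyses will be conducted for 6- and 12-months".
- The interaction step: "We will explore interactions between the covariate (baseline measure) and group to determine whether adolescents with lower baseline scores differentially benefit from the program".
- The main effect: "Assuming no interaction is found, we will examine the main effect of group assignment on the outcome measure after adjusting for baseline".
- A further model: "We will also conduct repeated measures ANCOVA models to examine differences in the effect of the intervention on primary outcomes", comparing the 6- and 12-month time points.

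Specific Aim 2 carries the approach over to quality of life: "We will use the same ANCOVA models described above to examine the effects of the intervention on general and weight-specific QoL".

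Section 16 does not say how strong an interaction must be to count as found. It also does not say what is estimated or tested if one is found.

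**The concern.** The result readers will look for is the intervention-versus-usual-care difference in 2-hour glucose. As written, the data decide whether that difference is examined. If the preliminary test is positive, the protocol offers no estimate, contrast or model in its place, and the analyst must choose one after seeing the data.

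The condition resembles the textbook parallel-slopes check for ANCOVA. In a randomised trial that check is not needed for the average effect to be meaningful. The step can therefore remove the main result without protecting against any bias. The loss is most likely when the effect depends on baseline, which is the pattern the interaction step is meant to look for.

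**Working it through.** **Inputs from the protocol.** Section 5 expects about 300 screened and about 40% with raised 2-hour glucose: 300 × 0.40 = 120, which reproduces the enrolment figure. There is no power calculation to reproduce. Section 16 gives two analyses of 2-hour glucose, one at 6 and one at 12 months.

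**Assumptions, because the protocol states none of these.** Two-sided 5% level for both the interaction test and the main effect; 1:1 allocation; standardised baseline; baseline slope 0.4; average effect 0.5 SD. Residual SD is 1, or 0.92, which is √(1 − 0.4²) and gives a control-arm outcome SD of 1. Analysed n is 120, or 96 as an example of 20% loss (120 × 0.8).

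**Step 1: does the condition protect anything?** Write the mean outcome as a + b·x + τ·G + δ·x·G, with baseline x centred at its overall mean and G the group indicator. The average effect is τ + δ·mean(x) = τ, because mean(x) = 0. Randomisation gives both arms the same expected baseline distribution, so the ANCOVA without the product term also targets τ. A non-zero δ means the effect varies around that average. It does not make the average wrong.

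**Step 2: withholding by chance alone.** With δ = 0, each analysis has a 5% chance of a positive interaction test. For at least one of the two 2-hour glucose analyses, if they were independent, the chance is 1 − 0.95² = 9.75%. They share participants, so independence is only an approximation.

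**Step 3: withholding when the effect varies with baseline.** The standard error of the interaction is about 2σ/√n, so z = δ√n/(2σ) and the chance of a positive test is about Φ(z − 1.96). For δ = 0.3, σ = 1, n = 120: z = 0.3 × 10.954/2 = 1.643, and Φ(−0.317) = 0.376. Simulation (15,000 runs per row) puts it slightly lower, because it uses the t distribution and sampled baselines:

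| Slope difference (SD per SD), n = 120 | Main effect withheld, residual SD 1 / 0.92 | Significant main effect if always examined | Significant main effect under the plan's rule |
|---|---|---|---|
| 0 | 5% / 5% | 77% / 84% | 73% / 79% |
| 0.1 | 9% / 9% | 78% / 84% | 71% / 76% |
| 0.2 | 19% / 22% | 77% / 83% | 63% / 65% |
| 0.3 | 36% / 42% | 77% / 82% | 50% / 48% |
| 0.4 | 57% / 64% | 76% / 82% | 33% / 30% |

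Reversing the sign of the interaction changes nothing beyond simulation error: at −0.3 the main effect is withheld in 36% / 41%, and at −0.4 in 57% / 64%. With 96 analysed it is withheld in about 29% to 35% at 0.3 and 47% to 54% at 0.4.

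**Step 4: type I error.** With an average effect of zero and n = 120, the two-step rule rejects in about 5% of runs with no interaction and in about 2% to 5% with slope differences of 0.1 to 0.4. Always examining the main effect rejects in about 5%.

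**The case against.** **It may be only a routine model check.** Section 16 also states the hypothesis and the ANCOVA comparison without any condition, and it calls the interaction step exploratory. The authors may well intend to report the adjusted difference regardless. That is a fair guess at intent, but the only sentence that says when the main effect is examined is conditional, and nothing shown supplies the other branch. Nor is this simply detail that a separate analysis plan would fill in: the protocol states the rule itself.

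**Other group comparisons carry no condition.** A reader might infer that the trial could end with no group comparison at all. That goes too far. The repeated-measures ANCOVA is unconditional, and the cost-effectiveness ratio in Aim 4 needs a difference in 2-hour glucose. However, the first is planned to compare the effect between time points and the second is an economic ratio. Neither is designated as the primary contrast.

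**Error control.** A reader might infer that a data-dependent choice of analysis inflates the false-positive rate. Step 4 shows that the rule as written does not. Inflation would need some unplanned replacement analysis, and the protocol specifies none to assess.

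**Which youth benefit.** A reader might infer that the result is lost mainly when higher-risk youth benefit most. The interaction test is symmetric, so the loss is equally likely if lower-risk youth benefit most.

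**Direction of the wording.** The stated aim is to "determine whether adolescents with lower baseline scores differentially benefit from the program". Low 2-hour glucose is the healthier end, so one might call the direction reversed. But the sentence serves several outcomes, and low insulin sensitivity is the worse end. This is loose wording and does not alter the interaction test.

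**Size.** The percentages depend on assumed values. A slope difference of 0.4 favouring high-baseline youth, with a baseline slope of 0.4, would mean that baseline predicts nothing in the intervention arm. That is a strong scenario, and nothing in the protocol supports or excludes it. At 0.1 the main effect is withheld in only about 9%.

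**Conclusion.** The point stands in this form: the main effect of group on the primary outcome is conditional on a preliminary test that has no threshold and no defined alternative, and the same condition reaches quality of life. The missing branch is plain from the text and rests on no assumption. The size does rest on assumptions (120 analysed, 1:1 allocation, two-sided 5% test, residual SD 0.92 to 1). The main effect is withheld in about 5% of analyses with no interaction (9.75% for at least one of the two 2-hour glucose analyses if independent), about 35% to 42% at a slope difference of 0.3 and about 57% to 64% at 0.4. These last two ranges fall if fewer are analysed. The harm is lost power and an undefined primary estimand. Claims of inflated type I error, or of a problem specific to high-risk youth, are not supported. The change should be made.

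**What to change.** In section 16, Specific Aim 1:

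1. Delete the opening conditional clause of the main-effect sentence. State that the baseline-adjusted group difference, with baseline centred at its overall mean, is the primary result in all cases. Aim 2 then inherits the corrected rule.
2. Report the baseline-by-group interaction as a separate exploratory analysis, with estimated effects and intervals at chosen baseline percentiles (for example the 25th, 50th and 75th). Say that it does not determine whether the main effect is reported.
3. As a minor wording point, replace the reference to low baseline scores with worse baseline values: higher for 2-hour glucose, lower for insulin sensitivity.

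The cost is a rewording of two sentences. No new data, visits or participants are needed.
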